**Introduction and rationale**

Dengue fever (DF) is the most common vector-borne viral disease of humans, with more than 100 million cases recorded each year in tropical and subtropical countries and an increasing incidence in more temperate regions. Over half of the world’s population live in areas at risk of infection. In its most serious forms, dengue haemorrhagic fever (DHF) and dengue shock syndrome (DSS), it is also a major cause of morbidity and mortality, particularly in Southeast Asia where it is the principle reason for paediatric admission to hospital during the rainy season. In VietNam over the past three years we have noted an increasing incidence in adults. Data from dengue protein crystallographic studies have revealed opportunities to intervene in the replication cycle of dengue viruses (DENV). The pH-dependent structural changes involving the fusion loop in the envelope protein are central to successful virion fusion with the endosomal membrane and release of infectious viral nucleic acid into the cytoplasm (1). Chloroquine, a safe and pharmacologically well-characterized drug, inhibits several viruses requiring a pH dependent step for cell entry (2)(3). The in vitro inhibitory concentration (IC50) for chloroquine against dengue viruses is ~5 M (Fig. 1 from Novartis Institute for Tropical Diseases, Singapore). Furthermore, chloroquine inhibits the normal proteolytic processing of certain dengue virus proteins thereby reducing the infectivity of the mature virions (4). Following a 3-day course of therapeutic oral doses of chloroquine (600mg base on days 1 and 2, then 300mg base on day), the peak drug concentration (Cmax) ranges from 0.1 to 0.3g/mL (~0.3-1M) in plasma and 1 to 1.2g/mL (3.2-3.8M) in whole blood. Chloroquine is extensively sequestered in the tissues. In animals, from 200 to 600 times the plasma concentration may be found in the liver, spleen, kidney, and lung (5, 6). In humans, the highest concentrations of approximately 100M were measured in the marrow, liver, spleen and leukocytes (7). These data suggest a therapeutic potential for chloroquine in dengue-infected patients since the Cmax in relevant organs is likely to exceed the IC50 value. This trial asks the question whether chloroquine, by its action on the acidification of the intracellular vacuole, reduces viral load in patients with dengue.

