#### Sample Size

The following assumptions were made in calculating the sample size for EF study:

1. The median time to NS1 and PCR clearance in dengue population with normal standard of care is 72 hours
2. Most (90%) of dengue patients admitted to the trial will be day 3 of illness
3. The average proportion of cases that are NS1 and/or PCR positive on day 3 is 80%
4. At the end of follow-up (5 days after study entry), 20% of cases will still be positive for NS1
5. 10% of patients lost to follow-up

Under these assumptions, the minimum number of NS1 or PCR clearance cases required to be able to detect a 36 hours reduction of median time in Chloroquine arm as compared to standard care arm with a power of 0.8 and type I error 0.05--equivalently a hazard ratio relating to NS1 clearance of 2—is 72. Therefore total number will be 138/{0.8*(1-0.1)*(1-0.1)} =220 or 110 patients in each arm. The effect size in this sample size calculation study is large, but can be justified on the basis that a smaller effect size is unlikely to be clinically significant.

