#### Observations and Investigations

A full history and clinical examination will be performed at study entry and every day during the inpatient period. All clinical data will be documented in the case record form. The following investigations will be performed;

1. Chest X-ray or ultrasound on day of defervescance.
2. Hct, white cell count/differential, platelet count, SGOT, SGPT daily
3. Twice daily viral culture from plasma for minimum 5 days
4. Twice daily quantitative viral PCR from plasma for minimum 5 days
5. Twice daily assessment of Dengue NS1 levels for minimum 5 days
6. Twice daily measurement of plasma concentrations of the pro-inflammatory cytokines TNF, IL-6, IL-1B, IL12, IL-8 and the anti-inflammatory, IL-10 for minimum 5 days
7. ELISPOT assays to quantitate DENV-specific T cell responses
8. Microarray and PCR investigations to measure the effect of chloroquine on host gene-expression responses during acute disease

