**Blood sample collection**

Venous blood (2ml) will be collected from all cases twice daily for a minimum of 5 days after starting treatment. This 2ml sample is sufficient to evaluate viral and haematological parameters. At the time of discharge, a 5ml blood sample will be collected to measure dengue-specific T cell responses.

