**Subgroup analysis**

The following sub-group analyses will be performed:

1. Comparison of primary and secondary outcomes for those with primary or secondary dengue
2. Comparison of primary and secondary outcomes for each DENV serotype
3. Comparison of primary outcome for cases with DENV viraemias >10,000 cDNA equivalents per ml at the commencement of treatment
4. Comparison of primary outcome for cases with NS1 antigenaemias >500ng/ml at the commencement of treatment
5. In subjects with at least 4 consecutive positive RT-PCR, we will determine the slope of the line representing changes in viral load over time.

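### The viral-load slope is restricted to patients who stay PCR-positive for about 36 hours on treatment, so a between-arm slope comparison would be biased, most likely toward no effect, if chloroquine works

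*Protocol*

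**What the plan says.** The Protocol's Introduction and rationale closes by asking whether chloroquine "reduces viral load in patients with dengue". Observations and Investigations, item 4, provides the data to answer that: "Twice daily quantitative viral PCR from plasma for minimum 5 days". The Blood sample collection section places the samples "twice daily for a minimum of 5 days after starting treatment".

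The primary endpoints (Study Aims; Analysis plan, primary endpoints) reduce these data to times to a negative NS1 and a negative RT-PCR. The listed secondary endpoints do not include viral load. Viral load over time appears only in the Subgroup analysis section, item 5: "In subjects with at least 4 consecutive positive RT-PCR, we will determine the slope of the line representing changes in viral load over time".

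Items 3 and 4 of the same list define their viraemia and NS1 subgroups by values when treatment begins. Item 5 has no such anchor, and the protocol does not say what happens to patients with fewer than four consecutive positives.

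**The concern.** Whether a patient has four consecutive positive PCRs is known only after treatment has been given, and it depends on how quickly the virus clears. Clearance is what the drug is meant to change. If chloroquine speeds clearance, more patients fall out of the chloroquine arm than out of the control arm, and many of those lost are its steepest decliners. The patients left in the two arms are no longer comparable by randomisation.

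What is at stake is a real antiviral effect being understated or missed in the one analysis that uses viral load as a quantity. That is the form in which the introduction poses the trial's question.

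**Working it through.** **1. The plan's own figure.** The Sample Size section assumes "The median time to NS1 and PCR clearance in dengue population with normal standard of care is 72 hours". It aims to "detect a 36 hours reduction of median time in Chloroquine arm as compared to standard care arm", which puts the chloroquine median at 72 − 36 = 36 h. It calls this "equivalently a hazard ratio relating to NS1 clearance of 2", "with a power of 0.8 and type I error 0.05", and arrives at 72 events. Freedman's formula with two-sided alpha (sidedness is not stated) gives (1.96 + 0.84)² × (2 + 1)²/(2 − 1)² = 7.85 × 9 ≈ 70.6, or 71 events, which reproduces the stated 72 to within one. Equating halved medians with a hazard ratio of 2 is exact under exponential clearance (72/36 = 2), so I use that model in step 3.

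**2. When the rule is met.** At 12-hour spacing, four positives counted from the entry sample fall at 0, 12, 24 and 36 h. If the entry sample is not counted, they fall at 12, 24, 36 and 48 h.

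**3. Share kept in each arm.** P(still positive at t) = 0.5^(t/median).

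| Fourth positive at | Control (median 72 h) | Chloroquine (median 36 h) |
|---|---|---|
| 36 h | 0.5^(36/72) = 70.7% | 0.5^(36/36) = 50.0% |
| 48 h | 0.5^(48/72) = 63.0% | 0.5^(48/36) = 39.7% |

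At 36 h the rule drops 29.3% of control and 50.0% of chloroquine patients. With the plan's yield factors, evaluable patients per arm are 110 × 0.8 × 0.9 × 0.9 ≈ 71, leaving about 50 control and 36 chloroquine patients.

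**4. Effect on the slope difference (illustrative).** The protocol gives no distribution of loads or slopes, so the following are assumptions:
- log10 load falls linearly;
- starting load averages 4 log10 above the detection limit, with SD 0.75 or 1.5;
- individual slopes are log-normal with coefficient of variation (CV) 0.2, 0.4 or 0.6;
- the correlation of starting load with slope is 0, 0.5 or 0.9;
- control median clearance is close to 72 h;
- a patient is kept if clearance takes longer than 36 h.

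This makes 2 × 3 × 3 = 18 settings, each with 400,000 patients per arm. The result is the between-arm difference in mean slope among those kept, divided by the true difference.

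| Drug effect on slope | Settings attenuated | Ratio there | Other settings |
|---|---|---|---|
| 1.5 times steeper | 15 of 18 | 0.40 to 0.98 | 3 at 1.00 to 1.10 |
| Doubled | 17 of 18 | 0.25 to 0.97 | 1 at 1.19 |

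Three of the doubled-slope settings, in log10 per day:
- SD 0.75, CV 0.4, correlation 0: true difference 1.437, among those kept 0.722, ratio 0.50.
- SD 0.75, CV 0.6, correlation 0.9: true 1.553, among those kept 0.394, ratio 0.25.
- SD 1.5, CV 0.2, correlation 0.9: true 1.360, among those kept 1.617, ratio 1.19.

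The third setting reverses because the rule also removes patients who start with a low load. When load and slope rise together and slopes vary little otherwise, those patients are the slow decliners.

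With no drug effect, selection is the same in both arms and the difference is unbiased.

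The simulated clearance times are less spread out than exponential ones. In the doubled-slope settings the rule therefore keeps 81% to 100% of control patients, against 71% in step 3, and 37% to 49% of chloroquine patients. The imbalance appears under either model, but its size depends on the model.

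**The case against.** - **No comparison is written.** Items 1 to 4 each announce a comparison, whereas item 5 says only that a slope will be determined, with no contrast or test. This stands: the between-arm comparison is an inference from the section heading and the two-arm design. Slopes merely described by arm would, however, carry the same selection.
- **The analysis plan may settle it.** Fitting method and handling of undetectable values can properly be left there. The four-positive condition is different: the protocol already fixes it, and a later document would have to override it.
- **A minimum number of points is an ordinary estimability rule.** That is a fair reason for requiring it when a line is fitted to each patient. It does not make the resulting set suitable for comparing arms.
- **The direction and size are not certain.** A reader might infer that the rule always pulls the comparison toward no effect, or by a known fraction. The documents support neither. They give no starting loads, slopes or correlation between them, and the ratio exceeds 1 in a few settings.
- **The antiviral question is answered elsewhere.** Both primary endpoints are analysed in patients with detectable NS1 or virus at entry, without the four-positive rule, so an effect on clearance would still be tested. This stands and limits the consequence.

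**Conclusion.** The point holds as a defect in a stated rule. Item 5 selects patients after randomisation on a function of a primary endpoint. At the plan's own effect size, with exponential clearance assumed, it keeps about 71% of control and 50% of chloroquine patients (63% and 40% if the fourth positive falls at 48 h).

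If the drug works, a comparison of slopes in this set is biased, most likely toward no effect. The estimated difference would be roughly 0.3 to 1.0 of the true one in most settings tried, and up to about 1.2 when starting load varies widely and is correlated with slope. These ratios rest on assumed loads and slopes and are illustrative only.

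A reader might also infer that the rule can create a spurious benefit for an inactive drug, or that it compromises the trial's main result. Neither follows: there is no bias when the drug has no effect, and the primary analyses do not use this set. The point deserves correction because item 5 is the only analysis of viral load as a quantity in the protocol shown.

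**What to change.** Replace the four-positive condition with all randomised patients who are PCR-positive in the pre-dose sample. Estimate the between-arm difference in log10 viral-load slope with a mixed model that has a treatment-by-time term and treats values below the detection limit as left-censored. State the between-arm comparison explicitly. Fast clearers then stay in, and the set is defined at baseline, in line with items 3 and 4.

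The cost is somewhat more analysis work on data already being collected, with no extra samples. The model also relies on linear decline and on distributional assumptions, which matter most for patients with few quantifiable values. The individual slopes in patients with four or more positives can be kept as a descriptive summary. Moving the analysis to the secondary endpoints is optional and not needed to remove the selection.

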**Hospital costs**

For patients in the study, the OUCRU will pay hospital costs that are consistent with routine care of uncomplicated dengue.

**Figure 1. Activity of chloroquine against Dengue Virus (NGC) in CFI assay**

CFI assay:

-1

1 da

2 daysddays

0

Cell seeding

1. Virus infection;

1. ELISA to detect viral E protein production;

2. Fluorescent endpoint assay to measure cytotoxicity of testing compounds

(day)

Day-1. Seeding of 20,000 cells into 96-well microtiter plates

Day 0. Infection of cells with NGC at MOI=0.3 in the presence of chloroquine (0.039 ~ 20uM in 2X series dilution);

Day 2. Virus load is measured by quantifying the amount of E protein produced using ELISA. IC50s are calculated by GraphPad Prism V.3.02. In addition, the amount of viable cells are quantified using fluorescent endpoint assay(propidium iodine staining).

**Figure 2. KPM survival analysis of a pilot study of chloroquine use in dengue patients. Shown is the proportion of adult patients (n=20) with NS1 antigenaemia since beginning randomised treatment (chloroquine or placebo).**
